**Methods/design:**

GERT is a one-armed single-center phase I/II trial. In a first step, dose-escalation of TMZ from 50 mg/m^2 ^to 75 mg/m^2 ^together with radiotherapy and cetuximab will be performed. Should safety be proven, the phase II trial will be initiated with the standard dose of 75 mg/m^2 ^of TMZ. Cetuximab will be applied in the standard application dose of 400 mg/m^2 ^in week 1, thereafter at a dose of 250 mg/m^2 ^weekly. A total of 46 patients will be included into this phase I/II trial.

Primary endpoints are feasibility and toxicity, secondary endpoints are overall and progression-free survival. An interim analysis will be performed after inclusion of 15 patients into the main study. Patients' enrolment will be performed over a period of 2 years. The observation time will end 2 years after inclusion of the last patient.

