### Study objectives

Primary endpoint of the study is feasibility and toxicity of combined trimodal therapy with TMZ, cetuximab and radiotherapy. According to the current standard treatment for patients with GBM, about 10% off all patients develop WHO Grade III and IV toxicity [9]. We defined a toxicity rate of 30% for WHO Grade III and IV side effects as overall acceptable for this study.

Secondary endpoints include overall survival, progression-free survival and quality of life.

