### Patient selection

Inclusion criteria into the study protocol include:

- patients ≥18 and < 70 years of age

- Karnofsky Performance Score ≥60

- histologically confirmed supratentorial GBM

- interval between primary diagnosis and registration for the study < 4 weeks

- patients will be included according to the incidental gender distribution for patients with GBM of ♀/♂ 2:3

- adequate blood values (not older than 14 days prior to initiation of RCHT)

- neutrophil count (ANC) ≥1500/mm3 or white blood cells (WBC) ≥2000/mm3

- platelets ≥100.000/mm3

- hemoglobin ≥10 g/dL

- BUN <1.5 times the upper range

- Total and direct bilirubin <1.5 times the upper laboratory limit

- Adequate liver enzymes <3 times the upper laboratory limit

- Life expectancy >12 weeks

- Written informed consent

Additionally, the combined treatment with radiotherapy and TMZ would be the standard treatment recommended to be performed in the patients included into the study.

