### Statistical calculations for trial sample size

The trial is evaluating in its Phase 1 part the tolerability of the TMZ dose of 75 mg/m^2 ^together with cetuximab in a two step escalation with a maximum of 12 patients, while evaluation in its Phase II part the following two hypotheses:

1. non-tolerable toxicity H0: existence of no tolerable toxicity, i.e. TR >30%, NTR ≤70%

2. tolerable toxicity H1: existence of tolerable toxicity, i.e. TR < 10%, NTR ≥90%

with RT denoting the rate of toxicity and NTR the rate of non-toxicity. Therefore, the trial consists of a dose finding part (Phase I) and a feasibility part (Phase II).

These two hypothesis will be examined using a two-step optimal phase II design according to Simon et al. [30] in the defined patient population with a significance level of 5% (alpha = 0.05) and a power of 90% (beta = 0.1) with a one-armed analysis in this single arm trial.

To demonstrate tolerability of the toxicity with a hypothesis-test between NONTOX of 70% versus the anticipated NONTOX of 90% within a One-Step-Phase II Design, 36 evaluable patients are required (NCSS PASS 2000).

We calculated a drop-out rate of 10%, and therefore a projected patient number of 40 is planned.

With inclusion of the 6 patients for the dose-finding part of the protocol, a maximum of 46 patients will be included into the study.

Recruitment will be carried out over 2 years and a follow-up time of 1 year per patient is required to evaluate the primary endpoint.

Overall survival will be determined as the time span between primary diagnosis and death of lost to follow-up (censored observation). Progression-free survival will be determined as the time span between start of the treatment and tumor progression or death, whatever occurred first or an event which characterises a censored observation.

The trial consists of a dose-finding study (part 1; Phase I) followed by a Phase II component.

#### Step 1

3 patients are treated with combined RCHT (RT at dose level 1 (DL1) with a total dose of 60 Gy in 2 Gy single fractions + TMZ 50 mg/m^2^/day, 6 weeks)

Cetuximab (ERBITUX^®^) is applied in a dose of 400 mg/m^2 ^in week 1, thereafter weekly at 250 mg/m^2 ^week during the course of RCHT.

Adjuvant treatment: 6 cycles of TMZ 150 mg/m^2^/day for 5 days, every 28 days (q28d)

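### Overall survival is counted from primary diagnosis and progression-free survival from start of treatment, so overall survival includes pre-entry time in which no enrolled patient can die

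*Protocol article*

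**What the plan says.** Both definitions stand next to each other in the protocol article, in the Methods/design section on statistical calculations for the sample size:

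- OS: "Overall survival will be determined as the time span between primary diagnosis and death", with loss to follow-up treated as censoring
- PFS: "Progression-free survival will be determined as the time span between start of the treatment and tumor progression or death, whatever occurred first"

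The list of inclusion criteria under Patient selection sets the timing of entry: "interval between primary diagnosis and registration for the study < 4 weeks". It also requires "Life expectancy >12 weeks".

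The role of the endpoints is given under Study objectives: "Secondary endpoints include overall survival, progression-free survival and quality of life". The abstract describes the design: "GERT is a one-armed single-center phase I/II trial".

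The article gives no reason for the two different origins.

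**The concern.** Patients enter the cohort at registration, not at diagnosis. Anyone who died between the two dates is not in the trial. For those who are in it, the interval from diagnosis to registration is survival time that could not have turned out otherwise, yet it is counted in OS. The length of that interval reflects how quickly a patient was referred and registered, not what the regimen did.

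The second difficulty is internal. Death is an event for both endpoints. If a patient dies without progression, OS and PFS should be the same length. Under the stated definitions they differ by the whole time from diagnosis to start of treatment.

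In a randomised comparison a common offset of this kind would largely cancel between the arms. This trial has one arm, so the offset goes directly into the reported median. The abstract names efficacy as part of the trial's goal, and OS and PFS are the endpoints that speak to it. Readers are likely to set the median beside the published ones in the Background section.

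**Working it through.** The plan states no target, power or sample size for OS or PFS, so there is no survival figure of its own to reproduce. The check has two parts: what the definitions imply, and how large the offset can be.

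**Part 1: the definitions side by side.** Let *g* be the time from diagnosis to start of treatment, and *t* the time from start of treatment to death, for a patient who dies without progression.

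- PFS = *t*
- OS = *g* + *t*
- Difference for the same death = *g*

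The gap *g* has two pieces. Diagnosis to registration is under 4 weeks by the inclusion criteria. Registration to start of treatment has no limit in the article.

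**Part 2: the size.** Inputs:

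- Diagnosis to registration: 0 to just under 28 days (Patient selection).
- Median OS values used only to set a scale: 12.1, 14.6 and 19 months (Background).
- Month length: 30.44 days.

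Cap on guaranteed time to registration: 28 / 30.44 = 0.92 months. At an assumed 2-week gap: 14 / 30.44 = 0.46 months.

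If all patients have the same gap, the median from diagnosis equals the median from entry plus that gap. If gaps vary, the shift is roughly the average gap.

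| Median from entry (months) | Read from diagnosis, 2-week gap | Read from diagnosis, 4-week gap |
|---|---|---|
| 12.1 | 12.56 (+3.8%) | 13.02 (+7.6%) |
| 14.6 | 15.06 (+3.2%) | 15.52 (+6.3%) |
| 19 | 19.46 (+2.4%) | 19.92 (+4.8%) |

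The 4-week column is the upper limit of the registration window, reached only if every patient is registered at the last moment.

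Measured against OS from start of treatment, the wait after registration adds to this. As an assumption, 6 or 8 weeks from diagnosis to treatment gives 42 / 30.44 = 1.38 or 56 / 30.44 = 1.84 months. A 14.6-month median from treatment start would then read 15.98 or 16.44 months.

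For 12-month survival, assume an exponential hazard after entry with a 14.6-month median:

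- From entry: exp(−ln 2 × 12 / 14.6) = 56.6%
- From diagnosis, 4-week gap: exp(−ln 2 × (12 − 0.92) / 14.6) = 59.1%

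**Scale against sampling error.** Assume exponential survival and that all 46 patients die. The 95% limits on the median are then the estimate multiplied by exp(±1.96 / √46), that is 0.75 and 1.33. Around 14.6 months this is about 10.9 to 19.5 months. The offset is much smaller than this, but it is systematic: it always lengthens OS relative to OS from entry.

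**The case against.** The strongest reply is that nothing in the trial is decided on OS. The hypotheses, alpha, power, patient numbers and interim rule all concern toxicity. OS has no threshold and no test. Both origins are written out openly, and because the definitions themselves require the dates, OS from another origin can be computed later. All of this stands, and it limits the weight of the point.

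Several stronger readings are tempting and should not be drawn:

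- **That OS is biased upward against the published medians.** The Background section does not give the time origins of those medians. If a comparator counted from diagnosis, the present definition matches it, and an entry-based OS would look shorter. If it counted from randomisation or treatment, the present definition flatters the trial. The article does not settle which applies.
- **That the offset is worth over a third of the temozolomide benefit.** Dividing 0.92 by 14.6 − 12.1 = 2.5 months gives 37%. That puts every patient at the limit of the window and divides by a between-arm difference that this single-arm trial does not test. The shift relative to the median is the fairer measure.
- **That the performance-status, life-expectancy and blood-value criteria add to the guaranteed time.** They select fitter patients whichever origin is used, and moving the clock does not remove that selection. Only the wait before entry is at issue.
- **That a delayed-entry (left-truncated) analysis is needed.** At the registration cut-off, it would differ from the ordinary Kaplan-Meier curve only if an enrolled patient died within about 4 weeks of diagnosis, while others had not yet entered. Given the life-expectancy criterion this should be very rare, and the two curves would almost coincide.

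Nor does the article plan an analysis of OS minus PFS, so the mixed clocks spoil no stated analysis of post-progression survival.

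What survives is narrower. The pre-entry time is in OS by definition, no control arm offsets it, and the two endpoints disagree on the timing of the same death.

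**Conclusion.** The point holds as a modest flaw in the definition of secondary endpoints. OS contains guaranteed time of at most about 0.92 months up to registration, plus an unstated wait to treatment. A median of 14.6 months from entry would read about 15.5 months at the cap and about 15.1 months at a 2-week gap. The 2-week gap is an assumption, as is a gap common to all patients, because the article does not give the actual distribution.

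That OS includes this time follows from the inclusion criterion and the OS definition alone. Whether the reported OS would be too favourable against any particular published series cannot be determined from the article. The toxicity design and its patient numbers are not touched. The correction is worth making because it is cheap and is more credible if fixed before the survival results are known.

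**What to change.** In the two sentences that define OS and PFS, use one origin at entry for both. Registration is preferable, because every enrolled patient has that date. If start of treatment is chosen instead, the text must say how registered but untreated patients are counted.

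Keep OS from primary diagnosis as a clearly labelled supplementary figure, so that the result can still be set beside series that use that origin.

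The cost is about one sentence. The dates needed are those that the eligibility criterion and the present definitions already require, plus the registration date. Patient numbers, visits and treatment do not change. The downside is that the headline median OS becomes a few weeks shorter. If registration is used, PFS becomes longer by the wait from registration to treatment.

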## Background

Glioblastoma multiforme (GBM) is the most frequent primary malignant brain tumor in adults. Until recently, the standard treatment approach in patients with GBM was neurosurgical resection, as radical as possible, followed by postoperative radiotherapy (RT). However, in spite of technical advances in surgery and radiotherapy, overall survival still remained unsatisfactory with median overall survival times of 9–12 months [1,2].

Over the last decade, a number of clinical investigations on combined radio-chemotherapy (RCHT) after neurosurgical resection have been conducted. A large randomized trial performed by the Neuro-Oncology Working Group of the German Cancer Society evaluated combined RCHT with nimustine plus teniposide versus nimustine plus cytarabine and could obtain a median overall survival time of 16.5 months in patients with GBM [3]. Temozolomide (TMZ), an oral alkylating agent, had demonstrated antitumor activity as a single-agent treatment in recurrent GBM [4-6].

In a pilot phase, the feasibility of concomitant administration of TMZ and fractionated RT followed by 6 cycles of adjuvant TMZ was demonstrated and one could suggest that this combined treatment modality would offer significant benefit for patients with GBM [7]. At the Department of Radiation Oncology at the University of Heidelberg a trial evaluating combined RCHT with TMZ in a dosage of 50 mg/m^2 ^5 days per week was conducted, without adjuvant application of TMZ; we observed a median overall survival time of 19 months, and treatment-related toxicity was low [8].

A large randomized trial conducted by the EORTC evaluated the outcome after combined RCHT with TMZ followed by adjuvant TMZ application as opposed to RT alone; in patients treated with RCHT, overall survival was significantly increased to 14.6 months as compared to RT alone with 12.1 months [9].

Treatment-related toxicity was relatively high in the combined treatment arm with 14% of patients presenting with WHO Grade 3 or 4 hematologic toxicities as compared to 7% in the RT-group. Additionally, RT was interrupted or delayed in 32% of the RCHT-patients, and only 47% of all RCHT patients completed the planned 6 cycles of adjuvant TMZ-application. However, the significant increase in overall survival can be considered a major progress and thus the current standard for patients with GBM is considered RT together with the concomitant and adjuvant application of TMZ.

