If 2 out of 3 patients develop DLT, the study will be stopped. If 1 out of 3 patients develops DLT, three more patients will be included at a dose of 50 mg/m^2 ^TMZ. Dose escalation is halted if two ore more patients develop DLT.

#### Step 2

3 Patients are treated with combined RCHT (RT with GD 60 Gy, ED 2.0 Gy + TMZ 75 mg/m^2^/day, 6 weeks)

Cetuximab (ERBITUX^®^) 400 mg/m^2 ^in week 1, thereafter at a dose of 250 mg/m^2 ^weekly during RCHT.

Adjuvant treatment: 6 cycles of TMZ 150 mg/m^2^/day for 5 days, every 28 days (q28d).

If DLT occurs in one patient additional three patients will be treated at DL 2. If 2 or more patients develop DLT, DL 1 will be the recommended dose for the phase II part of the study the study.

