### Interim analysis

An interim analysis is planned after inclusion of 15 patients into the main study. The trial can be stopped should it be obvious that the alternative hypothesis of a tolerable toxicity rate

H1:R≤10% i.e. NONTOX-Rate ≥90%

cannot be achieved, i.e. should the number of WHO grade III and IV toxicities be larger than 7 (meaning 8 or more Grade III and IV toxicities). In this case the study will be closed due to "futility".

Recruitment for the study will be conducted during a period of 2 years. Final evaluation of the primary and secondary endpoints of the study will be performed 1 year after inclusion of the last patient.

The formal end of the study is defined as the end of the observation period of the last patient included into the study.

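### Dose level 1 can enter Phase II on 0 DLTs in 3 patients after dose level 2 has failed; completing six patients first is a cheap, modest safeguard

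*Protocol article*

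**What the plan says.** All rules are in the protocol article, under *Statistical calculations for trial sample size* unless noted.

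- **Step 1 (DL1).** Three patients receive radiotherapy, cetuximab and TMZ 50 mg/m². Two DLTs in three stop the study. "If 1 out of 3 patients develops DLT, three more patients will be included" at that dose, and "Dose escalation is halted if two ore more patients develop DLT". With 0/3 there is no expansion and the trial escalates.
- **Step 2 (DL2).** Three patients receive the same regimen with TMZ 75 mg/m². One DLT brings three more. "If 2 or more patients develop DLT, DL 1 will be the recommended dose for the phase II part of the study".
- **Size.** Phase I is planned "in a two step escalation with a maximum of 12 patients". Phase II has 36 evaluable patients, 40 planned, and is designed with "a significance level of 5% (alpha = 0.05) and a power of 90% (beta = 0.1").
- **Next printed decision point** (*Interim analysis*). After 15 Phase II patients the trial can be stopped "should the number of WHO grade III and IV toxicities be larger than 7", that is, at 8 or more.
- **Earlier experience at this centre** (*Background*). With radiotherapy and TMZ 50 mg/m², "we observed a median overall survival time of 19 months, and treatment-related toxicity was low". That trial gave no adjuvant TMZ, and cetuximab is not mentioned.

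**The concern.** DL1 and DL2 differ only in the concomitant TMZ dose. Radiotherapy, cetuximab and adjuvant TMZ are the same in both steps, so a failure at DL2 also casts some doubt on DL1. Yet on the 0/3 route the fallback dose goes to as many as 40 Phase II patients on the evidence of three.

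Elsewhere the plan uses six patients: a level with one DLT in three is expanded to six, and DL2 is given up at two or more DLTs. The same check is not applied to DL1 at the moment when it becomes the dose carried forward. If DL1 were in fact too toxic, the article prints no rule that would force a decision before patient 15. What is at stake is the exposure of the first Phase II patients in this branch, much more than the trial's final conclusion.

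**Working it through.** **Inputs from the document.** Cohorts of 3, expanded to 6 after one DLT; 40 planned and 36 evaluable Phase II patients; 10% drop-out; 70% versus 90% non-toxicity; interim stop at 8 or more of 15.

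**Assumptions.** The document gives no DLT rates, so a range of rates *p* is shown. Patients are independent. The interim look counts patients with a toxicity. Where Phase II figures appear, DLT is taken to equal grade III/IV toxicity.

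**1. The plan's own figures.** Phase I maximum: 6 + 6 = 12. Phase II: 36/0.9 = 40. Total: 40 + 6 = 46. All reproduce.

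**2. What 0/3 shows.** Exact one-sided 95% upper limits for the DLT rate:
- 0/3: 1 − 0.05^(1/3) = 0.632
- 0/6: 1 − 0.05^(1/6) = 0.393
- 1/6: 95% quantile of Beta(2, 5) = 0.582

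**3. How often the branch occurs.** P(0/3 at DL1) = (1 − p)³. P(DL2 fails) = P(2 or more of 3) + P(1 of 3) × P(1 or more of the next 3). The product is the chance of Phase II at DL1 on 0/3.

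**4. What the added rule does.** After 0/3, DL1 is given up if 2 or more of the next 3 have a DLT: 3p²(1 − p) + p³.

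| Assumed DL1, DL2 rate | P(0/3 at DL1) | P(DL2 fails) | Branch | Stop, given branch | Stop, all trials |
|---|---|---|---|---|---|
| 10%, 30% | 0.729 | 0.506 | 0.369 | 0.028 | 0.010 |
| 20%, 40% | 0.512 | 0.691 | 0.354 | 0.104 | 0.037 |
| 30%, 50% | 0.343 | 0.828 | 0.284 | 0.216 | 0.061 |
| 40%, 60% | 0.216 | 0.918 | 0.198 | 0.352 | 0.070 |

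At 10% and 20% the stops are wrong stops. At a 30% rate the rule misses 1 − 0.216 = 78% of cases in the branch.

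**5. Stopping by patient 15, without and with the added rule.** An exact search for the Simon optimal design (70% versus 90%, alpha 0.05, power 0.90) gives 15 patients in stage 1 and 36 in all, stopping at 4 or more toxicities of 15 and accepting at 6 or fewer of 36. This is compared with the printed 8-of-15 rule.

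| Interim rule | 30% rate | 40% rate |
|---|---|---|
| 8 or more of 15 (printed) | 0.050 → 0.236 | 0.213 → 0.433 |
| 4 or more of 15 (Simon) | 0.703 → 0.720 | 0.909 → 0.915 |

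**6. Phase II error rates in this branch, without and with the added rule.** The article prints no final boundary, so 6 or fewer of 36 is used in both rows.

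| Interim rule | Power at 10% toxicity | Acceptance at 30% toxicity |
|---|---|---|
| 8 or more of 15 (printed) | 0.937 → 0.916 | 0.054 → 0.051 |
| 4 or more of 15 (Simon) | 0.905 → 0.889 | 0.046 → 0.045 |

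**The case against.** The strongest reply is that nothing here is wrong. The rule is complete and consistent: DL1 passes on 0/3 or 1/6 and is the fallback. A stricter rule can always be proposed. That stands, and it is why this is a suggestion and not a correction.

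Most of the gain in stopping by patient 15 exists because the 8-of-15 look is weak. With 4 or more of 15, which helps in every branch, the extra stopping almost vanishes and what remains is an earlier stop. That also stands.

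Toxicity is documented weekly and before each cetuximab dose (*Adverse events*), so early events would be seen. True, but the article ties no decision to them before patient 15. The full protocol may hold further stopping rules or confirm the fallback dose in other ways. The article does, however, print the fallback as a fixed instruction.

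Three stronger readings are tempting, and the documents support none of them:
- *DL1 would be unsafe, since its DLT rate could be 63%.* That is an upper limit from 0/3 taken alone, not an estimate. The centre's own experience with 50 mg/m² points the other way, though it does not cover the combination with cetuximab and adjuvant TMZ.
- *The Phase I maximum of 12 shows that six patients at DL1 were intended and then forgotten.* Twelve is simply the case in which both levels are expanded after one DLT.
- *The trial could reach a false conclusion.* The chance of accepting a 30% toxicity rate moves only from 5.4% to 5.1%.

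**Conclusion.** The point holds as a low-severity improvement to patient safety. The fallback can carry DL1 into Phase II on 0/3, directly after a closely related regimen has failed, with no printed decision point before patient 15.

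The benefit is a decision after 3 patients instead of 15. It changes the outcome in about 6% to 7% of all trials at assumed DL1 rates of 30% to 40%. *Study objectives* calls a 30% grade III/IV rate acceptable (a different endpoint), and the null hypothesis places non-tolerable toxicity above 30%, so the clear benefit lies above 30%. Nothing changes when DL1 had one DLT in three, because six patients have then already been treated there.

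The Phase II comparisons rest on equating DLT with grade III/IV toxicity and, for the final analysis, on a boundary that the article does not print. Correcting the interim boundary would matter more than this change.

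**What to change.** Add to the Step 2 fallback rule:

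> *If only three patients have received DL 1, the first three Phase II patients at DL 1 complete a group of six. Further enrolment waits until their DLT assessment is complete. If 2 or more of the six have a DLT, Phase II is not continued at DL 1.*

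Count these three within the planned 40, so that no patients are added.

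**Cost, in this branch only:**
- One enrolment pause of at least the 6-week RCHT period, longer if the DLT window (not given in the article) is longer.
- Wrong stops in about 3% of cases at a 10% DLT rate and 10% at 20%.
- About 2 points of power: it stays above 90% under the printed interim rule (0.916). Under the Simon boundary it falls just below (0.889), and the power should then be restated.

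If that loss is not acceptable, count the three in Phase I. This stays within its maximum of 12 (6 + 6) but costs three more patients.

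Separately, the statement that "a maximum of 46 patients will be included into the study" already fails without this change when DL2 fails after expansion (3 + 6 + 40 = 49). It should be raised as its own point.
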